## Abstract

Background: Trunk impairment produces disorders of motor control, balance and gait. Core stability exercises (CSE) are a good strategy to improve local strength of trunk, balance and gait. Methods and analysis: This is a single-blind multicenter randomized controlled trial. Two parallel groups are compared, and both perform the same type of therapy. A control group (CG) (*n* = 110) performs conventional physiotherapy (CP) (1 h per session) focused on improving balance. An experimental group (EG) (*n* = 110) performs CSE (30 min) in addition to CP (30 min) (1 h/session in total). EG is divided in two subgroups, in which only half of patients (*n* = 55) perform CSE plus transcutaneous electrical nerve stimulation (TENS). Primary outcome measures are dynamic sitting, assessed by a Spanish version of Trunk Impairment Scale and stepping, assessed by Brunel Balance Assessment. Secondary outcomes are postural control, assessed by Postural Assessment Scale for Stroke patients; standing balance and risk of fall assessed by Berg Balance Scale; gait speed by BTS G-Walk (accelerometer); rate of falls, lower-limb spasticity by Modified Ashworth Scale; activities of daily living by Barthel Index; and quality of life by EQ-5D-5L. These are evaluated at baseline (T0), at three weeks (T1), at five weeks (end of the intervention) (T2), at 17 weeks (T3) and at 29 weeks (T4). Study duration per patient is 29 weeks (a five-week intervention, followed by a 24-week post-intervention).

## 1. Introduction

Strokes have a high morbidity, and also result in up to 50% of survivors being chronically disabled. Thus, a stroke is a disease of public health importance with serious economic and social consequences [1]. Over 80% experience a balance disturbance in the subacute phase [2]. It reduces ability to perform daily tasks, and at six months after a stroke, 40% of stroke survivors have difficulties with basic activities of daily living (ADL), and 30% report participation restrictions, even at four years after a stroke [3].

This balance dysfunction is usually due to a combination of reduced limb, pelvis and trunk motor control, altered sensation (proprioception) of one side, and sometimes centrally determined alteration in body representation [4]. Trunk impairment is closely associated with postural imbalance and functional performance instability in gait [5] and in standing balance, increasing the risk of falls and fear of falling [6]. It can lead to reduction in independence to undertake ADL and reduced quality of life (QoL) [7].

Falls may have serious physical and psychological consequences, including increased risk of hip fracture (usually on the weaker side) and greater mortality and morbidity compared to people who have not had a stroke [8]. Fear of falling may lead to decreased physical activity, social isolation and loss of independence [9]. Any postural control disorder increases the risk of falling and injury [10]. Consequently, balance improvement is associated with decreased risk and fear of falling, as well as with improved QoL [11]. 

Balance is achieved through an interaction of central anticipatory and reflexive actions assisted by the active and passive restraints caused by the muscular system. The perception of verticality is based on the construction of a body-centred frame of reference in the gravitational environment. This frame of reference consists of afferent visual, vestibular information and somatosensory information of the body [12], which translate into an adequate motor response in order to guarantee both the anticipatory and adaptive aspects of balance control. In particular, the position sense of the trunk could be important to provide information about the alignment of the trunk in relation to gravity [13]. Trunk control and dynamic sitting balance are a fundamental requirement to be able to lead an independent life and to carry out ADL, such as combing, dressing or going to the bathroom. When walking, the human body is never balanced; most of the time the trunk is supported by one leg and the centre of mass “falls” onto the contralateral side. Therefore, trunk control in gait is an essential component [5].

Sitting lateral balance control appears to be the function critically affected by strokes, as well as the most sensitive to functional changes induced by rehabilitation [14]. Therefore, this will be the first goal to achieve with the neurorehabilitation treatment. Another aim is to achieve walking ability at discharge for minimising activity limitations and for maximising QoL. The control of the lower trunk, pelvis and leg muscles allows maintaining the centre of mass inside a stable base of support [15].

Rehabilitation is offered to all stroke survivors in the subacute phase after receiving initial medical treatment, in order to reduce their disability and accelerate their independence and resume ADL. An earlier and more intensive rehabilitation program in the early phase of a stroke is related to the good recovery of walking and functional independence status according to the concept “time is brain recovery” [16]. Furthermore, it is important to conduct rehabilitation trials during the initial days and weeks after a stroke, since it is then when spontaneous biological recovery takes place and when rehabilitation is delivered in the “real world” [17]. The first week until the first month post-stroke (acute and early subacute phase) is critical for neuroplasticity [18,19]. Recovery after a stroke follows a curve; it is not linear, with most of the improvement occurring during the first few days to six months [20]. 

A Cochrane systematic review concludes that 30 to 60 min per day delivered five to seven days per week is effective to recover function and mobility after stroke [21]. A good rehabilitation strategy, which might help improve trunk performance, trunk control and dynamic sitting balance [22], is approaches using trunk training therapeutic exercises [23] (today commonly known as Core Stability Exercises, or CSEs). Recent studies suggest that core strengthening plays a critical role in maintaining balance [24,25,26,27], functional mobility [28], gait, fear of falls and in improving anticipatory postural adjustment [29] in stroke survivors. Findings suggest that CSEs plus conventional physiotherapy has a positive long-term effect on improving dynamic sitting, standing balance and gait at three months after the end of treatment [30]. However, there is no consensus about which are the most effective intervention parameters, about intensity, and how early training exercises in the stroke subacute phase should be [31].

CSEs are voluntary movements that aim at promoting the neuromuscular control, coordination, strength and endurance of muscles that are central to maintaining dynamic stability of the spine and trunk. It is the ability to control the position and motion of the trunk over the pelvis and leg that allows optimal production, transfer and control of force and motion to the terminal segment in integrated kinetic chain activities [32,33]. It is essential to providing a solid base of core to exert or resist force, as it stabilizes the pelvis and spinal column for “proximal stability for distal mobility” [34]. Static core functionality is the ability of the core to align the skeleton to resist a force that does not change. The body core corresponds to the synergy 2, described by Israely et al. [35]. 

Several studies have shown that transcutaneous electrical nerve stimulation (TENS) applied to the trunk muscles during CSEs training could increase the motor output of trunk muscles. CSEs training combined with TENS could be more effective than CSEs alone for improving dynamic sitting balance [36]. TENS has shown to excite large sensory fibers, predominantly in the A-beta range through the cutaneous stimulation of muscles—it increases the excitability of the sensorimotor cortex [37].

Any intervention in the stroke subacute phase that reduces disability will probably be cost-effective. It should be noted that stroke rates are multiplied by 10 in the population over 75 years of age; this population usually suffers from sarcopenia, in addition to muscle weakness caused by strokes. For this reason, it is important to activate and strengthen the core muscles, since it has been shown that muscle atrophy and a significant impairment of postural reactive responses in the trunk rapidly occur [38]. This has led to shorter inpatient stays at the hospital becoming increasingly essential to have rehabilitation programs that are more efficient, which implies that patients have greater autonomy when discharged from hospital. 

There are few high-quality large multicenter randomized controlled trials (RCT) with patients recruited within 30 days after a stroke [39]. There is a clear need for larger trials conducted early after stroke in real-world clinical settings [40]. To determine the effectiveness, safety and optimal training parameters of CSEs, homogeneous post-stroke populations and follow-up measures are necessary [41]. 

The primary objective of this study is to evaluate the effectiveness of CSEs protocol (with and without TENS), in addition to conventional physiotherapy (CP) to improve dynamic sitting balance and gait (stepping) at short/mid-term in the subacute phase of a stroke. Secondary objectives are to evaluate the effectiveness of CSEs (with and without TENS) in addition to CP to improve postural control, standing balance, fall rate, risk of falls, gait speed, lower limb spasticity, ADL and QoL. Another secondary objective is to explore the sustainability of the effects of CSEs over time. It is important to know whether the treatment effects are sustainable over time, or if continuous therapeutic input is necessary to maintain the level of function even after being discharged (home).

## 2. Materials and Methods

### 2.1. Study Design and Setting

This study is an assessor-blinded, multicenter RCT, with a five-week treatment period followed by a three-to-six-month follow-up. It follows the consensus-based core recommendations from the stroke recovery and rehabilitation expert group [42] and the SPIRIT statement [43]. Participants will be randomly allocated (at a ratio of 2:1:1) to the control group (CG) (*n* = 110) or the experimental group (EG with and without TENS) (*n* = 110), <15 and >15 days after stroke. Patients are being recruited by inpatient rehabilitation hospitals in six centers in Catalonia: Hospital Universitari Parc Taulí de Sabadell; Hospital-Consorci Sanitari de Terrassa; Fundació Hospital de la Santa Creu de Vic; Hospital Sagrat Cor Germanes Hospitalaries de Martorell; Hospital Sociosanitari Mutuam Girona; and Centre Fòrum Parc de Salut Barcelona.

### 2.2. Recruitment

Treatments are randomly assigned using a computer program. To guarantee allocation concealment, treatments are assigned centrally via the web through Clinapsis^®^, an application designed to assist in the design and management of epidemiological and non-commercial clinical studies Clinapsis® Patients are recruited and screened for eligibility in three consecutive steps. Firstly, the principal investigator of each hospital is thoroughly briefed concerning the inclusion and exclusion criteria of the study, since they provide therapists with the information for possible inclusion. Secondly, the main researcher gives information about the study to potential participants, including the objective and description of the study, the duration, and risks and benefits. If the patients are interested in the study, an appointment is made to provide more detailed information and to answer questions. When the patient agrees to participate in the study, the informed consent is signed before obtaining the medical record, in order to guarantee privacy. Lastly, after obtaining informed consent, the patients are screened by the primary investigator to assure inclusion. 

After group allocation and before starting treatment (T0), pre-intervention tests are performed to assess the baseline values of primary and secondary outcome measures. At week 3, an assessment (T1) of only primary outcomes is performed. Within one day after completing the intervention (T2), data will be collected for all efficacy outcomes (see outcome measures section). The same data will be collected at three months after the end of the intervention (T3), and again at six months (T4). During the five-week intervention period, each session data will be collected regarding intervention adherence (number of sessions and duration), physiotherapy intensity, which exercises were performed for each patient and their incidences. All visits and efficacy assessments are performed at the rehabilitation center where patients have been initially treated for five weeks (whenever possible during routine clinical follow-up visits). Only when the patient is not able to personally attend the site due to a medical condition, the assessment takes place at home.

All data are recorded on-line using an electronic data form Clinapsis^®^, available from the study coordinating center. All investigators were trained in the use of the application and have a help guide, as well as a consultation service directly with the logistics coordinator of the study. Access to the study database is restricted to authorised study personnel by password.

For the calculation of the sample size, we have assumed that conventional rehabilitation will be associated with a clinically relevant change in the Trunk Impairment Scale at five weeks compared to the baseline. The minimal clinically relevant difference has been established as 3-point [44]. We have also assumed that rehabilitation by CSEs program will add a benefit of 1.6 points at five weeks, equivalent to 10% in the scale. That is, the experimental group with CSE will present a change of 4.6 points at five weeks with respect to the baseline situation (intragroup). Assuming a common standard deviation of 4 [45], and estimating a 10% lost at follow-up, accepting an alpha risk of 0.05 and a beta risk of less than 0.2 in a bilateral contrast, it will be necessary to include 110 patients in each group to detect a difference between groups of 1.6 points or higher on the total S-TIS 2.0 scale. The calculation of the sample size was done with the GRANMO program.

If a patient, either in CG or EG, has to withdraw from the treatment sessions due to a transient disease or mind trauma, he or she may be re-included if the dropout period is shorter than 10 days. Patients are allowed to withdraw from the study for any reason, and no adverse events have been described previously.

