### 2.3. Blinding

Due to the nature of the interventions, the study has a single-blind design. Therapists and participants cannot be blinded to treatment allocation. To avoid detection bias, efficacy outcomes are evaluated by an independent assessor blinded to the intervention. Each center has a therapist evaluator. They had a training day by principal investigator for the correct use of scales and questionnaires. This information is available online and in the paper. Furthermore, statistical analysis will be conducted, blinded to the allocation.

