### 2.7. Outcomes Measures

Primary outcome measures include: Dynamic sitting balance and coordination measured by S-TIS 2.0 [48]. This scale is a Spanish version of the Trunk Impairment Scale version 2.0 [55]. This scale aims to evaluate the trunk in patients who have suffered a stroke. The dynamic subscale contains items on the lateral flexion of the trunk and unilateral lifting of the hip. To assess the coordination of the trunk, the individual is asked to rotate the upper or lower part of his or her trunk six times, initiating the movements either from the shoulder girdle or from the pelvic girdle, respectively. There are two subscales; the first one has 10 items and the second one has six. The highest possible total score is consequently 16 points, which indicates an optimal dynamic sitting balance and sitting coordination. If the patient cannot maintain a sitting position for 10 s without back and arm support, with hands on thighs, feet in contact with the ground and knees bent at 90° (starting position), the total score for the scale is 0 points. This scale is utilised for inclusion criteria, and at T0, T1, T2, T3 and T4.Gait by stepping section of Brunel Balance Assessment (BBA) [56]. It is designed to assess functional balance for people with a wide range of abilities, and has been tested specifically for use post-stroke. There are three sections to the assessment: sitting, standing and stepping. In this study, only the stepping section is utilised. It consists of six levels to assess standing functional balance and a 5-m walk. At each level, the patient receives a score for his/her efforts. This gives an indication on whether the patient is improving within a level, even if he/she is not able to progress to the next level. The score also reflects how well the individual is functioning within that stepping section. The higher score is six points, and the individual is able to walk 5 m independently. Stepping is evaluated at T0, T1, T2, T3 and T4.

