### 2.8. Statistical Analysis

The main analysis population will be defined by intention-to-treat, comprising all randomised participants with a baseline assessment, regardless of later events such as protocol violations, missing data or loss to follow-up. Missing data will be imputed and the impacts of imputation on results will be explored. Secondary analyses will be conducted, restricted to the population of participants who followed the study protocol and had no missing data.

General linear models with repeated measures design will be used to test the effect of the Core Stability program (with or without TENS) on the change in the outcome of interest (total S-TIS 2.0 score or any other outcome) between the baseline and follow up (five weeks), using a repeated measures design with two levels (baseline, five weeks), as well as a two-level factor testing the intervention (usual care). The models will adjust for clinically relevant covariates, such as site, age, baseline levels of the dependent outcomes or severity of stroke. Similar models will be built to explore the effect of Core Stability at different time points (three months; six months). Similar models will test the effect of TENS added to Core Stability on primary and secondary outcomes, as well as primary and secondary endpoints.

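### The T0 baseline is taken after allocation in a trial that cannot blind participants, and the main analysis set is limited to patients who have it, so both the origin of change and the set depend on a post-randomisation step

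*Protocol article*

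**What the plan says.** Four parts of the protocol article bear on this point.

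- **Order of events (section 2.2):** "After group allocation and before starting treatment (T0), pre-intervention tests are performed to assess the baseline values of primary and secondary outcome measures". Nothing elsewhere places T0 before allocation, and section 2.6 labels T0 as the baseline.
- **Blinding (section 2.3):** "Therapists and participants cannot be blinded to treatment allocation". The safeguard is on the rater's side: "efficacy outcomes are evaluated by an independent assessor blinded to the intervention".
- **Main analysis set (section 2.8):** it is labelled intention-to-treat and described as "comprising all randomised participants with a baseline assessment, regardless of later events such as protocol violations, missing data or loss to follow-up". Section 2.8 adds: "Missing data will be imputed and the impacts of imputation on results will be explored".
- **Use of baseline (section 2.8):** the main model has two repeated levels, baseline and five weeks. On covariates: "The models will adjust for clinically relevant covariates, such as site, age, baseline levels of the dependent outcomes or severity of stroke".

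Section 2.7 says of the S-TIS 2.0: "This scale is utilised for inclusion criteria, and at T0, T1, T2, T3 and T4". It describes no eligibility use of the other primary outcome (BBA stepping) or of any secondary outcome.

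**The concern.** A baseline earns its place in the analysis because allocation cannot have influenced it. Here allocation already exists when T0 is done, and the article describes no step that withholds it from the patient until T0 is complete. S-TIS 2.0 and BBA stepping depend on the patient's performance, and the EQ-5D-5L is self-reported. If knowledge of the arm moves these scores, the movement enters the treatment effect through the change from baseline, the quantity on which the trial is sized.

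The second strand is the analysis set. Requiring a baseline assessment would be harmless if the baseline came before randomisation, because every randomised patient would have one. When it comes after, the requirement selects on a post-randomisation event. Someone who learns the arm, declines and leaves before T0 is removed. The clause about later events protects only those already in the set, and imputation cannot restore a person outside it.

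**Working it through.** **Reproducing the plan's figure.** Inputs from section 2.2: difference 1.6, SD 4, two-sided alpha 0.05, power 80%, 10% loss.

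- n per group = 2 × (1.96 + 0.842)² × 4² / 1.6² = 98.1, rounded up to 99.
- 99 / 0.9 = 110, as stated. Power at 99 evaluable per group is 80.4%.

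The sample size is not in dispute.

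**Illustration 1: an arm-related shift in T0 S-TIS 2.0.** The shift, the slope and the null effect are assumptions; the document supplies none of them.

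Let d be the shift in mean T0 between arms caused by knowing the allocation. The absolute bias is d for change scores and b × d for ANCOVA, where b is the slope of outcome on baseline. Take b = 0.5 with equal SDs, so the correlation is 0.5. The change-score SD is then 4 × √(2 × (1 − 0.5)) = 4, the same as the raw SD.

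- SE, change score: 4 × √(2/99) = 0.569.
- SE, ANCOVA: 4 × √(1 − 0.25) × √(2/99) = 0.492.
- Type I error = P(|Z + bias/SE| > 1.96).

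| Shift d | Change-score bias | Type I | ANCOVA bias | Type I |
|---|---|---|---|---|
| 0.25 | 0.25 (16% of 1.6) | 7% | 0.125 (8% of 1.6) | 6% |
| 0.5 | 0.5 (31% of 1.6) | 14% | 0.25 (16% of 1.6) | 8% |

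Both columns are shown because section 2.8 names baseline as a repeated level (a change-score comparison) and also, among example covariates, as an adjuster. A change score adjusted for its own baseline gives the ANCOVA effect.

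The bias can run either way. If the true effect is 1.6 and the bias is against it, change-score power falls from 80% to 66% (d = 0.25) or 49% (d = 0.5).

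**Illustration 2: exclusion for lack of T0.** If a fraction f of one arm is excluded and their mean change differs by D from those who remain, that arm's mean moves by f × D. With f = 5% and D = 2 to 4 points (assumed), the bias is 0.05 × 2 = 0.1 to 0.05 × 4 = 0.2 points, or 6 to 13% of 1.6. Excluding 2 to 5% of both arms, or 5 to 10% of one arm, on top of the 10% loss leaves power at 78 to 80%. The power cost is therefore small; the issue is selection.

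**The case against.** The case against a stronger reading is good, and much of it stands.

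- **Knowledge of the arm at T0 is not documented.** A reader might infer that every patient knows the arm when T0 is done. The article says only that T0 follows allocation and that patients cannot be blinded; a patient might learn the arm at the first session. The risk is conditional.
- **The shifts are assumed.** T0 precedes treatment, a blinded assessor scores it, a patient who cannot hold the starting position scores 0 whatever the effort, and both arms receive an hour of active therapy. A large shift is not the natural expectation, and the upper figures are not estimates of this trial's error rate.
- **Assessor unblinding at T0 adds little.** A reader might infer that early contact compromises the assessor. The same unblinded patients meet the assessor at T1 to T4 after weeks of known treatment, so moving T0 would not remove that risk.
- **The set is stated openly and may lose few people.** Someone who leaves before T0 will usually have no later outcome either, and imputing such a patient adds little information and does not cure informative departure. Section 2.7 also has a subsection on baseline assessment that lists characteristics taken mainly from records, so the condition could be read more loosely. But sections 2.2 and 2.6 tie baseline to T0, which is the natural reading.
- **The eligibility S-TIS 2.0 is only a partial rescue.** It covers one of two primary outcomes. It may come from the investigator who screens rather than the independent assessor, and the article does not establish that it is recorded apart from T0.

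None of this changes the stated order of events or the stated definition of the set. This is not detail left to a fuller document: the article fixes both.

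**Conclusion.** The point holds as a design weakness that should be fixed. By the article's own text, the baseline used as the origin of change and as a covariate is measured after allocation without participant blinding, and the set called intention-to-treat is a modified one conditioned on that measurement. Patients may, not must, know their arm at T0.

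The size of any bias cannot be derived from the document. The range of 6 to 8% (ANCOVA, slope 0.5) or 7 to 14% (change scores) rests wholly on an assumed shift of 0.25 to 0.5 points, with SD 4, 99 per arm and no true effect. The exclusion bias of 0.1 to 0.2 points is likewise assumed. The figures show that a modest shift would matter against a 1.6-point target; they do not show that one occurs. Site and age as covariates are unaffected.

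**What to change.** **Patients still to be enrolled.** Complete T0 and lock it in the electronic form after consent and confirmation of eligibility, and before the web system releases the allocation. Section 2.2 runs allocation and data capture through the same application, so this reorders existing steps.

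**Analysis set.** Define the main population as all randomised participants, analysed in the arm assigned, with no condition on a baseline assessment. Impute missing baselines along with the other missing data, and report by arm the number randomised without T0.

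**Patients already randomised.** Section 2.1 says recruitment is under way, so reordering cannot help them. Where a separately recorded pre-allocation screening S-TIS 2.0 exists, use it as the baseline covariate in a sensitivity analysis for that outcome only. No pre-allocation score is described for BBA stepping or the secondary outcomes.

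**Cost.** A few T0 assessments will be done on patients who are then not randomised, the form needs a sequencing rule, and section 2.8 needs a revised definition. The sample size stays at 110 per group.
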